## Abstract

**Background:**

There is much discourse in healthcare about the importance of client-centred rehabilitation, however in the realm of community-based therapy post-stroke there has been little investigation into the efficacy of goal-directed practice that reflects patients' valued activities. In addition, the effect of active involvement of carers in such a rehabilitation process and their subsequent contribution to functional and emotional recovery post-stroke is unclear. In community based rehabilitation, interventions based on patients' perceived needs may be more likely to alter such outcomes. In this paper, we describe the methodology of a randomised controlled trial of an integrated approach to facilitating patient goal achievement in the first year post-stroke. The effectiveness of this intervention in reducing the severity of post-stroke depression, improving participation status and health-related quality of life is examined. The impact on carers is also examined.

**Methods/Design:**

Patients (and their primary carers, if available) are randomly allocated to an intervention or control arm of the study. The intervention is multimodal and aims to screen for adverse stroke sequelae and address ways to enhance participation in patient-valued activities. Intervention methods include: telephone contacts, written information provision, home visitation, and contact with treating health professionals, with further relevant health service referrals as required. The control involves treatment as usual, as determined by inpatient and community rehabilitation treating teams. Formal blinded assessments are conducted at discharge from inpatient rehabilitation, and at six and twelve months post-stroke. The primary outcome is depression. Secondary outcome measures include participation and activity status, health-related quality of life, and self-efficacy.

**Discussion:**

The results of this trial will assist with the development of a model for community-based rehabilitation management for stroke patients and their carers, with emphasis on goal-directed practice to enhance home and community participation status. Facilitation of participation in valued activities may be effective in reducing the incidence or severity of post-stroke depression, as well as enhancing the individual's perception of their health-related quality of life. The engagement of carers in the rehabilitation process will enable review of the influence of the broader social context on recovery.

**Trial registration:**

Australia and New Zealand Clinical Trials Register (ANZCTR): ACTRN12608000042347

## Background

Inroads in the efficacy of acute stroke management have resulted in reduced mortality rates and morbidity from the event of stroke. However, stroke remains a leading cause of death, and the rise in life expectancy of the Australian population (with the proportion of the population aged over 65 years having considerably increased) has resulted in a higher prevalence of stroke, with an estimated 60 000 events occurring per year [1,2]. About 320 000 people (aged between 16-85 years) had suffered a stroke in 2007 in Australia, with a large subset (42.5%) reporting a disability that resulted in ongoing activity restriction [2]. Disability caused by stroke has enduring social and economic consequences, in part due to the burden on the healthcare system and the dependency on carers for physical and financial assistance [3]. It is important to continue to address the management of the sequelae of stroke, not just in the acute and immediate sub-acute settings, but into the longer-term chronic phase. There is a need to determine and develop strategies that may facilitate longer term outcomes and maximise an individual's capabilities.

Early post-stroke rehabilitation tends to focus on the amelioration of impairments and activity restrictions, so that basic mobility and self-care tasks can be achieved. Upon returning to the community, further sub-acute rehabilitation resources may be required to maximise recovery and prevent deterioration [4,5]. Surprisingly, research on the most effective way to further assist the patient and their carers to re-establish their lives in the community during the first year after stroke, especially with regard to the resumption of valued activities, is scant. Most people who have had a stroke display ongoing activity limitations (such as problems with basic self-care tasks and mobility), and also a resultant negative impact on domestic and community-based activities [3]. There can also be alterations in participation levels, health-related quality of life (HRQoL), and mood status. Variables such as these may reflect the concept of adaptive functioning, and can provide an important gauge of an individual's perception of their current situation [6].

Alteration in mood status, particularly in the form of emerging depression, is a common problem post-stroke. It is estimated that a third of people who have had a stroke will display post-stroke depression (PSD) [7]. Depression is characterised by persistent low mood (of a duration greater than two weeks), often with addition symptoms of: alterations to weight or appetite; disturbed sleep patterns; loss of energy; sense of worthlessness; suicidal ideation; anhedonia; psychomotor retardation and/or agitation. PSD has not only been associated with a diminished re-uptake of previously valued activities, but a reduced perception of HRQoL [8,9]. Thus, there is the need for interventions aimed at not only improving physical impairment and disability, but also addressing mood status, participation, and HRQoL [8]. This was highlighted in a recent systematic review which found that rehabilitation therapies, conducted in patients' community context, which endeavoured to frame the intervention to target patients' valued activities (such as leisure pursuits), showed moderate evidence for improvement in global participation measures and HRQoL [10].

Participation status can also be markedly affected post-stroke, with mobility problems and the presence of depressive symptoms being particularly predictive of adversely altering participation levels [11,12]. Participation, in this context, relates to a person's ability to engage in life situations [13]. This concept also encompasses aspects of personal and social re-integration, and a return to valued and meaningful activities [14]. Valued activities are an individual phenomenon, and may relate to life aspects such as: domestic, family, and social roles; employment; hobbies, socialising; and sporting pursuits [15]. Resumption of previously valued activities may also have an impact on an individual's sense of life quality [8,15]. The perception of HRQoL is generally reported to be reduced post-stroke [16,17]. The concept of HRQoL tries to capture how an individual views the impact of their health status on their quality of life, especially in relation to physical, cognitive, and emotional factors. Presence of depressed mood, low functional activity status, and lack of social support are predictors of HRQoL post-stroke [18,19]. However, a study by Sturm et al. (2004) ascertained that a significant number of people who have had a stroke report a diminished HRQoL despite an overall good functional recovery [8].

Central to the aim of the post-stroke rehabilitation process should be a client-centred framework that adopts a goal-setting model. Meaningful, collaborative goal-setting is an acknowledged essential part of rehabilitation practice [14]. Endorsement of goal-directed behaviour (by the patient, support network, and rehabilitation services) is an important element for ongoing recovery and overall adjustment to post-stroke abilities [20]. In addition, the process of goal setting may assist to reduce carer anxiety and offer active problem-solving coping strategies [21]. The need to provide long-term care for the person who has had a stroke can place carers under considerable emotional, financial, and physical stress [22]. To date, many interventions aimed at reducing the negative impacts of caring have shown minimal effect, and there is a requirement for a heightened understanding of the relationships between patient and carer characteristics, and overall carer outcomes [23]. Awareness of the impact of the broader social context, and in particular consideration of psychosocial factors (such as carer involvement and their emotional well-being) on rehabilitation outcomes is required. Carers can facilitate the recovery process, and their inclusion in the overall rehabilitation model is essential. In shifting to a rehabilitation paradigm that is consumer and carer-directed, there may also emerge a shift from a model based on clinician-driven rehabilitation programs to one that primarily aims to achieve patient-centred recovery.

The issues that are faced by the person who has had a stroke, and their family and carers, in the first year post-stroke are multifactorial and complex. The relationship that has been established in the literature between mood status, participation level, and HRQoL post-stroke warrants further investigation. The exploration of an integrated, goal-oriented approach (utilising activities that the patient nominates as important to their notion of recovery) is the basis of the intervention framework in this randomised controlled trial. The additional effect of such an intervention on the primary carer will also be investigated.

The objectives of the study are to:

(i). investigate the effectiveness of a client-centred, integrated approach to facilitating goal achievement and recovery in the first year post-stroke.

(ii). determine the effect of the integrated approach on carer outcomes.

This paper provides a detailed description of the methodology of this post-stroke interventional study, based on the following hypotheses:

- The primary hypothesis for the participants who have had a stroke is that an integrated approach to facilitating goal achievement in the first year after stroke will result in less depressed mood, as measured by the Geriatric Depression Scale (15 item) [24,25].

- For the carer participants, the primary hypothesis is that the integrated approach will result in an enhanced HRQoL, as assessed by the Assessment of Quality of Life (AQoL) [26].

## Method/Design

This is a single blind randomised controlled trial of a multifaceted, client-centred intervention for post-stroke management.

### Participants

All patients admitted to the inpatient hospital rehabilitation unit with the primary diagnosis of acute cerebrovascular accident (inclusive of cerebral infarction, intracranial haemorrhage, and subarachnoid haemorrhage) will be eligible to participate in this study provided informed written consent is obtained. Participants will be recruited from two rehabilitation units of a tertiary teaching hospital in Melbourne, Australia. Exclusion criteria are: primary cause of disabilities is a diagnosis other than stroke; associated head trauma (such as fracture); epidural and subdural haemorrhage; cerebrovascular event due to the presence of malignancy; discharge destination is to a high level care facility; rehabilitation inpatient length of stay of less than 4 days duration; and participant resides greater that one hour travel from the rehabilitation unit.

Patients with communicative and cognitive deficits will be eligible to be recruited to the study, provided a 'person responsible' grants written consent for participation. It is acknowledged that these participants may not be able to participate in all assessment components. However, exclusion of these participants would limit the generalisability of the trial, and also exclude potentially valuable information acquired from their carers. Patients with cognitive and communication deficits are also often significant consumers of healthcare resources [27]. Patients who are from culturally and linguistically diverse communities will also be eligible to participate in this study, with the assistance of interpreters.

Primary informal carers will be invited to participate in this study if it is envisaged that they will provide at least five hours per week assistance to the patient participant with personal, domestic, or community activities of daily living. Care services provided by formal agencies, trained professionals, or paid carers will not be considered in this trial.

### Procedures

The design of this study is depicted in Figure 1. Patient participants will be formally assessed at three timepoints (T1 = rehabilitation discharge, T2 = six months post-stroke, and T3 = twelve months post-stroke). The baseline assessment will be conducted by an experienced allied health clinician blind to group allocation. This assessment (T1) will occur after obtaining written informed consent, but prior to randomisation, using the following measures:

**Figure 1 F1:**
[figure not shown]
Study design - randomised controlled trial

- cognition, using the Mini-Mental State Examination (MMSE) [28]. The MMSE provides a screen for cognitive impairment based on a 30 point questionnaire. It assesses various cognitive functions including: orientation, registration, attention and calculation, recall, language, and visual-spatial ability. A score of ≤ 23 points can provide preliminary evidence of cognitive impairment [29].

- activity/functional status, using the Functional Independence Measure - motor component (FIM-motor) [30]. The FIM assesses the amount of assistance that a person requires when performing basic activities of daily living (on a 7 point scale). It has both motor and cognitive subscales, however, only the motor components (13 items) will be scored in this study.

- mood status, using the Geriatric Depression Scale - 15 items (GDS-15) [24,25]. The GDS-15 is a screening tool for depressed mood status. Fifteen questions are scored based on 'yes/no' answers. Adequate reliability, validity, and sensitivity parameters have been determined when the GDS has been applied to stroke populations [31].

- self-efficacy, using the Strategies Used by People to Promote Health questionnaire (SUPPH) [32]. The SUPPH rates the degree of confidence that a person has in conducting specific self-care behaviours. Each item is rated on a 5 point scale of confidence, with higher scores indicating greater self-care self-efficacy. The 23 item SUPPH will be used in this study, as the items have been modified for use with people who have had a stroke [33]. Three main subscales are assessed: coping, reducing stress, and enjoying life.

In addition, general demographic information will also be recorded at the T1 assessment, including: participant's age, side/site/type of stroke, past medical history and co-morbidities, history of depression, living arrangements, and availability of an informal carer.

Collaborative goal setting will be conducted at discharge by the treating inpatient rehabilitation team members using Goal Attainment Scaling (GAS) [34] for all participants. Inpatient rehabilitation staff will undergo training regarding goal setting principles and the application of GAS (inservice program, booklet, and competency questionnaire). Rehabilitation team members will specifically discuss with the patient (and carer, if available) what activities they participated in prior to their stroke and which of those activities could represent goals to be pursued in the first year post-stroke. The determination of relevant, new activities based on current activity status will also be considered. Goals can be set across the domains of body structure/function, activity status, and participation status, depending on the ability level of the individual. However, emphasis will be placed on setting goals that enhance home and community participation levels, and reflect valued activities according to the patients' preferences. Should the goals that are nominated by the patient be considered unrealistic by the rehabilitation team, efforts will be made to determine achievable, preliminary goals that provide the foundation for more complex goals. This will be done via discussions with the patient until a collaborative compromise is reached.

An assessor, who is blind to group allocation, will conduct interviews in the participants' place of residence at T2 (six months post-stroke) and T3 (twelve months post-stroke). The assessor will repeat the measures taken at T1 (GDS-15, MMSE, FIM-motor, SUPPH), and will also include the additional outcome measures of:

- participation, using the (1) the Activity Card Sort (ACS) [35,36] and (2) the London Handicap Scale (LHS) [37]. (1) The ACS aims to measure the impact of disability on participation status by quantifying the percentage level of retained and lost activities. Q-sort methodology is employed using photo cards that depict everyday activities over three occupational performance domains (household, social/educational, and leisure). The ACS-AUS (Recovery version) will be utilised in this study, which consists of 82 activities validated to the Australian population [36]. (2) The LHS aims to measure the level of participation restriction across the six dimensions of the WHO disability framework (mobility, physical independence, occupation, social integration, orientation, and financial self-sufficiency) 

- health-related quality of life, using the Assessment of Quality of Life (AQoL) instrument [26]. The AQoL measures five dimensions of Health Related Quality of Life (HRQoL): illness, independent living, social relationships, physical senses, and psychological well-being. The tool consists of 15 items, each with four response levels. The AQoL has shown to be sensitive to changes in health states, and Australian population norms are available [39].

There will also be documentation of which health and community services are utilised by the participants who have had a stroke at each assessment timepoint during the first year post-stroke.

The primary outcome measure for the participants with stroke is depressed mood, which will be assessed by the GDS-15. Secondary outcomes for the participants with stroke are: participation (ACS and LHS); HRQoL (AQoL), activity/functional status (FIM-motor); self-efficacy (SUPPH); and cognition (MMSE).

Carer outcomes will be collected at T2 and T3, which include the GDS-15, ACS, and AQoL, and the Zarit Burden Index (ZBI) [40]. The ZBI aims to measure carers' perception of their caring role, and the degree to which they feel burdened by that role. Twenty-two items are measured on a 5 point scale, and an overall burden score is formed (0 = no burden to 88 = severe burden). Concepts within the scale cover notions of personal life, social life, health, emotional well-being, and finances [40].

The Human Research Ethics Committees (HREC) of both St.Vincent's Hospital Melbourne and The University of Melbourne have granted approval for this project. Written informed consent will be required from patients and their informal carer. If a patient is unable to grant informed consent (for example, due to cognitive deficits, dysphasia, reduced level of alertness), then a 'person responsible' (as defined in HREC guidelines) is eligible to give consent.

### Randomisation

Participants will be allocated to the control or intervention group of the study by a member of the research team not involved in the assessment process, using a computer-generated random allocation sequence (in block sizes of six) - with further stratification based on the participant's admission FIM-motor score. Participants with an admission FIM-motor score of less than or equal to 46 will be stratified into a 'severe' group, whilst those patients who have a score of greater than 46 will be stratified into a 'mild' group [41]. Participants (patients and their carers) are blind as to which group they have been allocated. In the Patient Information and Consent form, all participants are informed that they will be contacted at two and six weeks post-discharge from inpatient rehabilitation. It is also outlined that the participants may be offered further opportunities to discuss their progress and receive additional therapy and/or community resources. Permission was sought and granted for limited disclosure regarding the two interventions from the HREC. Sealed opaque envelopes are used to conceal the allocation, and participants will be assigned in order of completed baseline data set obtained by an assessor blind to group allocation.

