All the standardised intervention components (listed above as numbers 1-10) will be conducted by the primary researcher, who is a senior physiotherapist experienced in neurological rehabilitation, and not involved in the assessments. Should additional interventions be required, referrals will be made to relevant healthcare resources with correspondence outlining the arising issue and a request for appropriate assessment and management (for example: assessment of community access options with consideration of utilising an electric scooter to enable greater outdoor distances; review of urinary incontinence by the catchment Continence clinic; request for the general practitioner to assess and manage a patient's evolving low mood).

Verbal support will be given to the participants and their carers at all contacts, including acknowledgement of achievements to date and encouragement to continue to pursue activities and goals. Verbal support will also particularly be offered to those participants who display evidence of low mood status. Intervention group participants will continue to receive usual care from health and community resources as deemed appropriate by their medical consultants and treating team. The telephone details for the researcher will be given to the participant at each contact point, with the recommendation to make contact with the researcher if they have any queries or concerns about their recovery post-stroke.

During the phone contacts and home visit, issues or 'flags' may emerge that give rise to the need for additional interventions. Table 1 outlines the guidelines for interventions in response to certain 'flags'. However, as the interventions are based on the arising needs of an individual participant, the interventions listed in Table 1 are not exhaustive, but rather a strategy for initial clinical decision making. 'Flags' may also be discerned during scrutiny of the outcome data that is collected at the blind assessments conducted at six months post-stroke. Some of the intervention options may not need to be exercised, as the current treating team may already be aware of the issues and be providing the relevant service.

**Table 1 T1:** Guidelines for interventions based on arising 'flags'

Domain	'Flags'	Intervention options

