### Power and sample size calculations

Power calculations for this study are based on nine month post stroke data (obtained six months post-intervention) for GDS-15, from a study performed by Lai et al. (2006) [43]. Based on a power of 80% and the criterion for significance set at 0.05 (two-sided), the proposed sample size is 55 participants for each arm of the study. This computation assumes that the mean difference between groups is -1.4 (corresponding to means of 2.0 versus 3.4) and the common within-group standard deviation is 2.6 (based on SD estimates of 1.8 and 3.2). Allowing for a 20% drop-out rate, the aim is to recruit 66 participants in each group, giving a total sample of 132 participants.

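### One fixed block size of six, with an interventionist who knows earlier allocations, could let a fully informed observer foresee up to a quarter of assignments

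*Protocol article*

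**What the plan says.** The Randomisation section of the protocol article describes allocation "using a computer-generated random allocation sequence (in block sizes of six"), "with further stratification based on the participant's admission FIM-motor score". The two strata are scores of 46 or below and scores above 46. Arms are equal: under Power and sample size calculations, "the proposed sample size is 55 participants for each arm of the study", raised to 66 per arm and 132 in total for drop-out.

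The person who allocates is described only as acting "by a member of the research team not involved in the assessment process". On concealment and order: "Sealed opaque envelopes are used to conceal the allocation, and participants will be assigned in order of completed baseline data set". The Procedures section puts consent and baseline first: "This assessment (T1) will occur after obtaining written informed consent, but prior to randomisation". It also states that "The baseline assessment will be conducted by an experienced allied health clinician blind to group allocation".

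Under Intervention group, the ten listed components "will be conducted by the primary researcher, who is a senior physiotherapist experienced in neurological rehabilitation, and not involved in the assessments". Several of them fall at the point of inpatient discharge.

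**The concern.** A sealed envelope hides the next assignment only if that assignment cannot be worked out from those already made. With one constant block size, the end of each block can be worked out by anyone who has followed the sequence.

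Here one person follows at least half of it. The primary researcher treats everyone in the intervention arm and begins at discharge, so that person's knowledge grows during recruitment. Control allocations follow by elimination for anyone who also has the list of randomised participants. Stratification does not hide the sequence from such a person, because there are only two strata and the score that defines them is taken on admission, before randomisation.

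What is at stake is selection. If someone with this knowledge could influence whether a patient is approached, or when the baseline data set is completed, patients with a better or worse outlook for mood could be steered towards an arm. The Statistical methods section adjusts for initial FIM-motor score, history of depression, length of stay and discharge GDS-15. That would remove only selection acting through those variables.

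**Working it through.** The article gives no figure for predictability, so there is none to reproduce. The inputs are the block size (6), the 1:1 ratio implied by equal arms, the two strata and the total of 132.

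**Block composition.** Equal arms give 3 + 3 per block, hence C(6,3) = 20 equally likely arrangements. The total of 132 corresponds to 132/6 = 22 blocks if all are filled.

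**Certain assignments.** Once three of one arm have been used, the rest of the block is known. The number of certain assignments is therefore the length of the final run of identical assignments:

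- at least 1: always, 20/20 = 1
- at least 2: 8/20 = 2/5
- at least 3: 2/20 = 1/10

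The expected number is 1 + 2/5 + 1/10 = 1.5 per block. The general formula for blocks of 2n agrees: 2n/(n+1) = 6/4 = 1.5. As a share, 1.5/6 = 25%; over the trial, 22 × 1.5 = 33 of 132. By block, 60% have one certain assignment, 30% have two and 10% have three.

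**Best guess overall.** Suppose the observer always guesses the arm with more places left, and tosses a coin when they are equal. Expected correct guesses are n + ½(4ⁿ/C(2n,n) − 1) = 3 + ½(64/20 − 1) = 4.1 of 6, or 68.3%, against 50% by chance.

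**What the 25% requires.** The observer must know the block size, the block start, the stratum and every earlier allocation in that stratum. If all allocations are known but the strata are ignored (two equal strata assumed, 132 participants, simulated), about 0.01% of assignments are certain and about 63% of guesses are correct.

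**Effect of varying the block size.** The varying designs were simulated with 66 assignments per stratum and 4,000 repetitions. The observer is assumed to know the set of sizes and the full history within the stratum. All sizes are assumptions.

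| Block sizes | Certain | Correct guesses |
|---|---|---|
| 6 (as planned, exact) | 25.0% | 68.3% |
| 4 and 6 | about 5.7% | about 69.0% |
| 4, 6 and 8 | about 2.3% | about 67.8% |

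For 4, 6 and 8 that is about 3 certain assignments in 132 (132 × 0.023). The guessing rate barely changes.

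**Price in balance.** The largest possible end imbalance within a stratum is half the largest block. It rises from 3 to 4 per stratum, or from 6 to 8 over both.

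**The case against.** The strongest reply is that no route from predictability to bias is shown. Concealment suffers only if whoever approaches patients, takes consent or controls entry has the knowledge listed above, and the article does not identify that person. An article may leave recruiter and envelope-holder to the full protocol, so its silence is not evidence of a fault. The stated safeguards are also real: broad eligibility, consent and baseline before randomisation, a blinded baseline assessor, opaque envelopes, and a sequence position set only when baseline is complete. This stands, and it is why 25% can only be called an upper bound.

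A reader might go further in four ways that the document does not support:

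- *The research team at large knows the allocations.* The assessors at all three time points are described as blind. Only the primary researcher, the allocator and, for controls, the clinician who telephones them need to know.
- *The interventionist is also the allocator.* Both are described as outside assessment, which does not separate the two roles but does not equate them either.
- *The block size was known on site.* The article prints it; nothing shows that recruiters had it during enrolment.
- *Goals could be set to suit a foreseen arm.* Goals are set by the inpatient treating team, who are not said to know the sequence.

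It is also fair to object that varying the blocks leaves the guessing rate at about 68%. That is correct. The case for the change rests on the certain assignments alone.

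What the reply does not remove is that a single constant block size is a stated choice, made in a trial where one person necessarily learns every intervention allocation.

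**Conclusion.** The point holds as a minor to moderate design weakness. One fixed block size of six within two strata leaves up to 25% of assignments, about 33 of 132, deducible in advance by a fully informed observer. The figure assumes 3 + 3 per block, filled blocks, and knowledge of block size, block start, stratum and all earlier allocations in that stratum. A reader might infer that concealment was in fact broken or that the trial is biased. The article supports neither: it does not show that whoever recruits had this knowledge or used it.

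**What to change.** For the assignments still to be made, generate a new list with block sizes drawn at random (for example 4, 6 and 8), keeping the same two FIM-motor strata and the 1:1 ratio. Withhold both the sizes and the fact of any particular block boundary from the site team, and report the sizes only after recruitment has closed.

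The cost is regenerating the remaining list and its envelopes and amending a sentence in the Randomisation section. Arm sizes may end slightly less equal, within the limits shown above. The planned sample size and the analysis model do not change.

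Because overall guessing stays near 68% for someone with the full history, it would also help to state in the full protocol that recruitment is separate from allocation and intervention delivery, if that is the case. This is a clarification; the recommendation does not depend on it.
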